**Fig 3 pone.0279021.g003:**
[figure not shown]
Examples of the different congruency conditions.

The internal conflict condition adds a piece of information that would indicate the opposite response in the other task of the same domain. In the example, the 3 is the relevant number, due to its position, as the participant is indicated to perform the Even/ Odd task (which is always based on the second number), but the other stimulus (, the 2) would require the participant to respond with the other response if the task were the Low/High task (the task for which, the first number is relevant).

The external conflict condition is similar, with the only difference being, that the non-relevant task is not from the same domain, but is one (and always only one) of the tasks from the other domain.

The final condition, internal & external conflict combines the two other conflict conditions, where both the other internal task and one (and always only one) of the external task, bias the participant towards an incorrect response.

In order to avoid participants using task-irrelevant cues as a strategy to increase performance (Logan & Zbrodoff, 1979) half of the trials will include congruent task-irrelevant stimuli and half of the trials will include task-irrelevant incongruent stimuli. Task irrelevant stimuli will always all be either congruent or incongruent. The downside of this is, that it becomes impossible, during trials with congruent task-irrelevant stimuli, to determine whether a correct or incorrect answer occurred due to the task-relevant or task-irrelevant stimulus. For any analysis that requires this, only the incongruent task-relevant trials may be used.

The locations of the relevant stimuli for the numeric tasks were chosen to be Low/High on the left and Even/Odd on the right for the following reason. Should participants perceive two single digits not as e.g. seven and one but as seventy-one, this would not change the responses. As the Even/Odd relevant number is located (right, or for this discussion 2.) it determines whether a number is odd or even, independent from the number to the left of it (that is to say, both 1 and 71 are odd numbers). In a similar way, the size of the first number is somewhat independent of the second number (7 is larger than 5, but 71 is also larger than any number in the fifties).

Trial Setup:

Each trial will begin with a fixation cross in the middle of the screen for 350-850ms (600ms with a 250ms jitter), followed by trial instruction (400ms). Finally, participants are presented with the stimulus (350ms), where they are able to respond with a keystroke. If participants take longer than 350ms to respond the stimulus disappears. Once a response is recorded, a new trial begins (See Fig 4).

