**Fig 2 pone.0279021.g002:**
[figure not shown]
Larger example of stimuli with cue relevant for Task 3.

During the task, participants have to perform consecutive trials, where the task and stimuli will change quasi-independently from trial to trial.

For each trial, participants are presented with 3 quasi-independent pieces of information. They are presented with an instruction for the current trial in form of the task name (eg. VERTICAL/HORIZONTAL, presented 300ms before the actual stimulus) and two stimuli in form of signs or numbers. Based on the stimuli and the instruction participants are instructed to then respond as fast as possible, using either the S or the L key on a keyboard (keys were selected as they are located at a comfortable distance on the keyboard, in order to avoid straining the hands of the participants, keys will be marked with stickers for participant ease).

In total there are 96 different conditions for each trial (4 Tasks * 3 Switching conditions * 4 Congruency Conditions * 2 Response types). However, as differences in performance of individual tasks, as well as response type, are not hypothesized to have any impact on the performance of participants, 12 main conditions remain.

*Task-Switching Conditions*:

Each trial (n) is classified into one of the three Task-Switching Conditions depending on the task in trial n-1. If the task remains the same, the trial is a repeat trial. If the task switches, but remains within the same domain (LOW/HIGH to EVEN/ODD or VERTICAL/HORIZONTAL to COLD/HOT and vice versa), it is considered an internal switch trial. Finally, switches from one domain into the other (LOW/HIGH or EVEN/ODD to either VERTICAL/HORIZONTAL or COLD/HOT and vice versa) are considered external switch trials.

Note that patterns in Task 3 are not clearly visible in the document, please refer to Fig 2.

*Congruency Conditions*:

Depending on the stimuli that are presented a trial may evoke different degrees of conflict as to the correct response required. This occurs when the **task-relevant information of the stimulus** indicates, that eg. response 1 is correct, while in the presence of a non-relevant cue biasing the response in the incorrect condition. Here 4 different conditions exist.

In the no-conflict condition, a stimulus only presents one piece of information, the relevant one. In Fig 3 the stimuli in the no-conflict condition provide no information relevant to each of the remaining 3 tasks.

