## 8. Randomization

Participants are not randomized (within-subjects design), however, the trials that participants will complete are quasi-random. That is to say, trials will appear in a random order, which ensures a balanced design and equal probabilities of each trial occurring.

Sampling Plan

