### KSS

The KSS was developed to measure subjective sleepiness at any given time. It is a simple 9-point scale ranging from “extremely 1 = alert” to “9 = extremely sleepy–fighting sleep”. The scale has been validated and used frequently and provides a simple and fast measure that at the same time provides a reliable result [39]. The scale is attached in Appendix 7 in S1 Appendix.

SPS:

SPF: The estimation of fatigue will be performed using the Samn-Perelli Fatigue scale (SPF; [40]). This scale consists of 7 points and is used in aviation to assess crew fatigue. The French version comes from a report by the International Civil Aviation Organization [41]), but has not been psychometrically validated (see Appendix 6 in S1 Appendix).

Ishihara Colorblindness Test:

The Ishihara test for colorblindness [41] encompasses stimuli, that can determine the degree as well as the type of colorblindness, a person has. It will be presented in printed form, using a validated version of the test made available by the US department of infectious diseases (see Appendix 9 in S1 Appendix). Participants will be informed, that for a medically accurate test, a licensed physician is required. Should the suspicion of colorblindness arise during the assessment participants will be informed and advised to seek out a medical professional.

**The St Mary’s Hospital Sleep Questionnaire** (QSN; [42]) will be used to estimate the quality of sleep on the previous night. A translated version of this questionnaire has been produced (see Appendix 10 in S1 Appendix). The scoring of this questionnaire is not standardized due to the use of Likert scales and free responses. In addition, two questions regarding caffeine consumption have been added to this questionnaire.

Analysis Plan

The Analysis will be performed using Mixed (Multi-Level) Regression, as this allows for accounting for the effects of participants as well as tasks.

A first mixed multilevel regression will be performed on the dependent variable of RT (in MS).

The **independent Variables** are Trialtype (3 Levels), Conflict (4 Levels), Conflict Congruency (Binary) and Response (Binary)

The **dependent variable** is RT (in MS).

Time on Task (Time since task onset) will be included as a **covariate**

In a second Mixed multilevel logistic regression accuracy will be analyzed.

The **independent Variables** are Trialtype (3 Levels) and Conflict (4 Levels) and Conflict Congruency (Binary)

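### The newly relevant dimension was a distractor on the previous trial in about 50% of internal but 25% of external switches; no listed model term records this, and it can bias H2.2 in either direction

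*Protocol article*

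**What the plan says.** Section 7 (Study design) builds the trial grid as "4 Tasks * 3 Switching conditions * 4 Congruency Conditions * 2 Response types". A trial's switching condition depends only on which task was performed on the trial before. The section describes a run of trials "where the task and stimuli will change quasi-independently from trial to trial", and section 8 (Randomization) adds that the order is random in a way "which ensures a balanced design and equal probabilities of each trial occurring".

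Under Congruency Conditions, the internal level "adds a piece of information that would indicate the opposite response in the other task of the same domain". At the external level the task that supplies the distractor "is one (and always only one) of the tasks from the other domain". At the combined level, "both the other internal task and one (and always only one) of the external task, bias the participant towards an incorrect response". The same section says that "half of the trials will include congruent task-irrelevant stimuli and half of the trials will include task-irrelevant incongruent stimuli".

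The Analysis Plan lists the independent variables for reaction time as "Trialtype (3 Levels), Conflict (4 Levels), Conflict Congruency (Binary) and Response (Binary"). The accuracy model has the first three. Both add time on task, participant and task, with a random intercept and AR1 or ARMA errors as the starting structure. No term describes the distractors shown on trial n-1.

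**The concern.** H2.2 is the central hypothesis: switch costs should be larger when the switch crosses domains. With Trialtype at three levels, it is tested by external minus internal switches. The two switch types should then differ only in task similarity.

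They also differ in the recent history of the dimension that becomes relevant. An internal distractor has one possible source, and that source is the task to which every internal switch leads. An external distractor has two possible sources, and an external switch leads to one of them. The participant is therefore more often asked to respond to a dimension just shown as irrelevant when the switch is internal.

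If that history affects speed or accuracy, part of its effect is counted as similarity. The error is systematic, so more trials or participants would not average it out.

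**Working it through.** **Inputs**
- Four conflict levels and three switching conditions (section 7). The plan's grid reproduces: 4 × 3 × 4 × 2 = 96 conditions, and 3 × 4 = 12 after collapsing over task and response type.
- Each conflict level has probability 1/4 (balance, section 8).
- Conflict on n-1 is unrelated to the task on n (described as quasi-independent; taken as independent).
- An internal distractor is present at 2 of 4 levels, with one possible source. An external distractor is present at 2 of 4 levels, with one of two sources. The rule for drawing it is not stated; assumed unrelated to the next task.

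**Step 1: exposure rate.** Let I = 1 if the task on n was a displayed distractor on n-1.
- Internal switch: P(I = 1) = P(n-1 internal or combined) = 2/4 = 50%.
- External switch: P(I = 1) = P(n-1 external or combined) × 1/2 = 2/4 × 1/2 = 25%.
- Repeat: 0%, because the relevant task is never its own distractor.

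A simulation of 2,000,000 trial pairs gave 50.0%, 25.0% and 0%.

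**Step 2: robustness of the 2:1 ratio**
- Incongruent distractors only: 25.0% v 12.5%.
- Three distractor levels without the no-conflict level: 66.7% v 33.3%.
- Seven equal conflict-by-congruency cells: 4/7 = 57% v 2/7 = 29%.
- One external task drawn 80% of the time, switch destinations balanced: still 50% v 25%.
- External distractor tied to the next task: the external rate could lie anywhere from 0% to 50%. Nothing in the article says that it is tied.

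**Step 3: effect on H2.2.** Let d be the mean effect of I = 1 on reaction time. Internal switches shift by 0.50d and external by 0.25d, so external minus internal shifts by 0.25d - 0.50d = -0.25d. The article gives no value for d, so the range is an assumption:

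| d (ms) | Internal | External | External minus internal |
|---|---|---|---|
| +40 | +20 | +10 | -10 |
| +10 | +5 | +2.5 | -2.5 |
| -10 | -5 | -2.5 | +2.5 |
| -40 | -20 | -10 | +10 |

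**Step 4: do the planned terms remove it?** No. Conflict and Conflict Congruency describe trial n, and I is set by the distractor on n-1. AR1 or ARMA errors model residual correlation, not a mean shift tied to Trialtype.

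**Step 5: which adjustment works?** I can be 1 only after a conflict trial, so it may pick up a general after-effect of conflict. Take an illustrative general post-conflict effect of 20 ms, with d = 0 and no similarity effect.
- *Restricting to I = 0.* Retained internal switches follow no-conflict (1/2) or external-conflict (1/2) trials, so 50.0% follow a conflict. Retained external switches follow none, internal, external or combined in proportions 1/3, 1/3, 1/6, 1/6, so 66.7% do. Spurious contrast: (0.667 - 0.500) × 20 = +3.3 ms.
- *Entering I alone.* Within internal switches, I = 1 raises the proportion after conflict by 1 - 0.500 = 0.500 (weight 0.5 × 0.5 = 0.25). Within external switches it raises it by 1 - 0.667 = 0.333 (weight 0.25 × 0.75 = 0.1875). Pooled: (0.125 + 0.0625) / 0.4375 = 0.429, or 8.6 ms wrongly credited to I. Spurious contrast: 8.6 × (0.50 - 0.25) = +2.1 ms.
- *Entering I with the n-1 conflict level.* The after-effect has its own term, and the contrast is recovered.
- *Restricting to trials after a no-conflict trial.* I = 0 throughout and the n-1 level is the same for both switch types, so the spurious contrast is 0.

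**The case against.** The strongest objection is that the harm is hypothetical. The article nowhere says that responding to a just-ignored dimension is slower or faster. Its Introduction describes interference from the previously active task set and retrieval of task-set parameters, and neither fixes a sign or size for this event. The exposure rates also rest on an unstated drawing rule, and the article points to a fuller online protocol that may constrain the sequence. No plan can list every lagged covariate, and section 17 already leaves room to explore one sequential effect, performance after errors.

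Much of this stands. A reader might infer that the imbalance slows only the similar side and so pulls H2.2 towards zero. The documents do not support that: external switches are exposed too, at half the rate, and facilitation would push the contrast the other way. Nor can the bias be expressed as a share of the similarity effect, because the article states neither quantity and the ratio would divide one assumption by another.

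What does not stand is treating the point as detail left to another document. The 2:1 ratio follows from the conflict levels as described, it falls on the main contrast, and the model terms are listed explicitly. An unknown sign does not make the contrast safe: a positive or a null H2.2 result could each be partly artefact.

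**Conclusion.** The point holds as a design imbalance that the listed models do not adjust for. The newly relevant dimension was a distractor on trial n-1 in about 50% of internal and 25% of external switches, and H2.2 shifts by -0.25d. The shift is 2.5 to 10 ms in either direction for an assumed |d| of 10 to 40 ms, and zero if d is zero. The same reasoning applies to the accuracy model on its own scale.

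This rests on equal conflict levels, independence between successive trials and an external distractor not tied to the next task. The 2:1 ratio survives the variations tried, apart from such a tie. The article's Introduction says that irrelevant cues are always incongruent, while section 7 makes half of them congruent; that needs reconciling, but it does not change how often a distractor is present. No conclusion about the direction of the bias is warranted.

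**What to change.** - From the logged sequence, tabulate by switch type how often the task on n was a displayed distractor on n-1. This replaces the assumed rates with actual ones.
- Add that indicator, split by whether the n-1 distractor was congruent or incongruent, to both models together with the conflict level of trial n-1. The indicator alone, or restriction to trials where it is 0, mixes in general post-conflict effects (Step 5).
- Report the H2.2 contrast adjusted for both.
- As a sensitivity check, report H2.2 on trials that follow a no-conflict trial.

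The cost is a few extra terms and no new data. Each participant gives 5 × 336 = 1,680 trials, so the loss of degrees of freedom is negligible. The sensitivity subset keeps about a quarter, 1,680 / 4 = 420 trials, or about 420 / 3 = 140 per switching condition if these are equally frequent. If trial-level noise dominates, its standard error is about √4 = 2 times that of the full analysis, so it should support the adjusted estimate and not replace it.

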After the arrival of the participant for the first session, the participant will be asked to complete the Ishihara colorblindness test, before filling in the informed consent and information sheets. The participant will be informed, that they are permitted to ask questions at any time, and are also asked in what language they would like to perform the task (French or English). They will then fill in the Demographics questionnaire, the Edinburgh Handedness questionnaire and a KSS as well as the SPS scale. Next, the participant will be familiarized with the DTS protocol, and perform a training session, until the participants have acquired an adequate level of skill in the task.

For the training session, participants will perform at least 5 blocks (96 trials each, 3,5 min without feedback, 4 minutes with feedback) of the DTS protocol. During the first block, participants will receive feedback following each trial, to increase their individual learning rates. Subsequent blocks will exclude the feedback to completely mimic the experimental conditions. Additional blocks of training may be added following the 5 blocks to ensure adequate task performance. Additional training may be added, if the last completed block of trials, still shows a significant improvement over the preceding trial. Additional blocks will only be added with the explicit consent of the participant.

After the training session, the participant will again fill in a KSS as well as an SPS scale.

The second session will be scheduled no longer than 14 days after the first session. The procedure of the second session is largely similar to that of the first session. Participants will perform a much shorter second training session intended to help the participant remember the task. Participants will complete half a block of trials (48 trials) with feedback and another half block without feedback. Next participants will fill in a KSS and SPS scale and perform the experimental DTS protocol as detailed above. Participants will complete 5 Blocks of 336 trials each. In between blocks participants will have a short break of 28 seconds as proposed by Lim et al., 2016, to avoid recovery from the TOT effects.

Upon completion of the task participants will again fill in the KSS and SPS scale, before being thanked for their participation and paid (See Fig 5).

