## 15. Data exclusion (optional)

To detect and reject outliers two steps will be implied. First trials with reaction times of above 5 seconds will be rejected and counted as misses. In addition, an outlier detection will be performed based on the interquartile range criterion. This will be done for trials grouped by condition.

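### As printed, a trial ends only on a key press and the 5-second limit is a data-exclusion rule, so rest within blocks is uncapped while rest between blocks is held to 28 seconds

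*Protocol article*

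**What the plan says.** **Section 7, Trial Setup.** Each trial has a "fixation cross in the middle of the screen for 350-850ms (600ms with a 250ms jitter), followed by trial instruction (400ms"), then a stimulus shown for 350 ms. On slow responses the text says: "If participants take longer than 350ms to respond the stimulus disappears". The rule for moving to the next trial is: "Once a response is recorded, a new trial begins". No other trigger is given.

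**Section 7, before the task-switching conditions.** On speed, the text says "participants are instructed to then respond as fast as possible". This is an instruction, not a limit enforced by the program.

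**Abstract and Section 10.** The Abstract names limited breaks as the means of inducing mental fatigue. Section 10 sets the session at 5 blocks of 336 trials and adds: "In between blocks participants will have a short break of 28 seconds". The stated reason is to keep time-on-task effects from recovering.

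**Section 15.** "First trials with reaction times of above 5 seconds will be rejected and counted as misses". An interquartile-range outlier step within each condition follows.

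**Section 16.** Missing trials are to be removed but are not expected, because of the design.

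**Analysis Plan.** Time since task onset is the covariate in the reaction-time (RT) model. The accuracy model may use time since onset, trial number, or both.

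**The concern.** The stimulus times out, but as printed the trial does not. A participant who is drowsy, distracted or wants a pause can leave the key unpressed, and the task waits. Rest between blocks is fixed to the second, while rest within blocks has no upper limit.

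Rejecting the long trial afterwards removes its reaction time. It does not remove any recovery carried into the trials that follow. In the RT model the elapsed-time covariate also keeps running through the pause, so resting counts as time on task. Both would tend to weaken the time-on-task slope for RT (2.4.1) and its interaction with switching (2.4.3).

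Section 15 raises a second problem. It both rejects the trial and counts it as a miss, without saying whether a miss enters the binary accuracy outcome as an error. If it does, a pause or a slow correct answer is scored like a wrong key. Should such trials become more common as the session goes on, the error trend for 2.4.2 would be inflated for a reason other than wrong decisions.

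**Working it through.** **Step 1: does the rest of the document fit an open response window?**

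Inputs: 96 trials in 3.5 min without feedback (Section 10); mean fixation 600 ms and instruction 400 ms (Trial Setup). Elsewhere Section 7 has the instruction "presented 300ms before the actual stimulus", so both lead times are used.

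- Time per trial = 3.5 x 60 / 96 = 2.19 s.
- Implied mean RT = 2.19 - 0.60 - 0.40 = 1.19 s, or 1.29 s with the 300 ms lead.
- If trials ended with the 350 ms stimulus, 96 trials would take 96 x (0.60 + 0.40 + 0.35) / 60 = 2.16 min, or 2.0 min with the 300 ms lead.

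No mean RT is stated, so the 3.5 min can be checked only for consistency. It fits a window that stays open well after the stimulus disappears. Sections 15 and 16 point the same way: an RT above 5 s can be recorded only if the program still accepts a response after 5 s, and a task that waits for a key produces no missing trials.

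**Step 2: planned rest against task time.** Assumption: experimental trials run at the pace of training trials without feedback, which Section 10 says mimic the experiment.

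- One block = 336 x 2.1875 s = 735 s = 12.25 min; five blocks = 61.25 min.
- Planned rest = 4 x 28 = 112 s, so the session is 3,675 + 112 = 3,787 s (63.1 min). Rest is 112 / 3,787 = 3.0% of it.

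**Step 3: how much pausing equals a planned break?**

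- One key press withheld 28 s beyond a normal response equals one break and costs one rejected trial.
- A trial held to exactly 5 s gives 5 - 1.19 = 3.81 s of extra rest (3.71 s with the 300 ms lead). A total of 28 s needs 28 / 3.81 = 7.3 trials, or 28 / 3.71 = 7.5, about 2.2% of a 336-trial block. The 5-second rule catches none of these; the interquartile-range step may remove some.

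**Step 4: illustration over the session, and what a 5-second cap would do.** The frequencies and the 7 s length are assumptions; nothing in the document supports a particular value. The capped column uses 3.81 s per trial.

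| Share of 1,680 trials held | Trials | Rest at 7 s beyond a normal response | Rest if capped at 5 s |
|---|---|---|---|
| 0.5% | 8.4 | 59 s | 32 s |
| 1% | 16.8 | 118 s | 64 s |

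At 1% the uncapped total slightly exceeds the planned 112 s. The cap brings it to 64 / 118 = 54% of that.

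**The case against.** **The detail may be out of sight.** The Trial Setup refers to Fig 4, a diagram of a single trial, and Section 7 opens with a link to the full task protocol. Neither is shown, and either could give a time-out. A miss in Section 15 might also mean a non-response at a 5-second limit. This stands as a limit on certainty: it cannot be asserted that the program has no deadline. What can be said is that the printed text gives a positive rule whose only trigger is a key press, and that Sections 10, 15 and 16 fit it.

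**The plan treats 28 s as too short for recovery.** If four such breaks do not undo fatigue, nothing in the document shows that one more, or a scatter of short pauses, would. This stands. Adding up pauses shows how much rest is uncontrolled, not that recovery occurs.

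**Frequency and bias are unknown.** Participants are told to respond fast. Responses held for less than 5 s late in the session would raise late RTs, steepening the slope for 2.4.1 unless the outlier step removes them, while recovery would flatten it. The net direction cannot be derived.

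**Long pauses are visible.** RT is recorded on every trial, so they could be counted by block afterwards. This stands, but counting does not restore control over rest.

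**A stronger reading is tempting:** that the missing time-out defeats the study's only fatigue manipulation. The document does not support it. Limited breaks are the stated means, but 1,680 trials over about an hour also induce fatigue, and sleepiness and fatigue scales before and after the task check it separately.

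**Conclusion.** The point holds as a gap in control, not as a demonstrated bias. On the printed text, the break limit is unenforced within blocks. A single withheld response can match a planned break, and 7 to 8 held trials per block can do so without triggering the 5-second rule. Effects 2.4.1 and 2.4.3 could be weakened. Effect 2.4.2 could be distorted if misses are scored as errors, which Section 15 leaves open.

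This rests on the pace implied by the training blocks and on no time-out appearing in Fig 4 or the linked protocol. If one does appear there, the remaining problem is narrower: Trial Setup and Section 15 must be brought into line with it, and misses still need a defined place in the accuracy model. The change is worth making before data collection, because control over rest cannot be recovered afterwards.

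**What to change.** **Section 7, Trial Setup:** end each trial at the key press or 5 s after stimulus onset, whichever comes first, and start the next trial automatically.

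**Section 15:** log a non-response at 5 s as an omission, exclude it from the RT model, keep it separate from wrong-key errors in the accuracy model, and report omissions per block.

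**Cost:** a small change to the task script and a few sentences of text. Responses slower than 5 s would no longer be recorded, but Section 15 already rejects them. The cap limits any one pause to under 4 s beyond a normal response at the implied pace. It does not prevent pauses shorter than 5 s, so it reduces uncontrolled rest without removing it.
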